#### Overload and Progression

Sixteen protocols in increasing levels of perturbations will be used in the intervention training programs (see Table 3). The level of perturbation in the first training session will be personalized based on the following cutoff value and will be set according to the participant single-step threshold in standing. The single-step threshold is defined as the minimum perturbation magnitude that evoked a single-step response during the pre-testing procedure (i.e., overload).

The BaMPer system (Figure 3) is used to evoke perturbations during walking. The BaMPer is composed of a moving platform and a motor that provides unannounced surface translation perturbations in ML and AP directions during hands-free treadmill walking, aiming specifically to improve reactive balance reactions. The perturbations are programmed in the machine and are provided unexpectedly in terms of timing for both training methods (random PBBT and block PBBT). For example, in the first training session, the unannounced perturbations for both training groups (random PBBT and block PBBT) will vary with 1–2 cm displacement, 0.1–0.5 m/s velocity, and 0.5–3.0 m/s^2^ acceleration (see Table 3). However, while in the random PBBT, the perturbations were in random order, i.e., four directions (right/left/forward/backward), the perturbation in the block PBBT group in a single training session is to one direction only. In both training programs, a gradual increase in the difficulty of perturbation levels in terms of surface displacement, velocity, and acceleration will be made according to the trainee’s ability (see Figure 2, Table 3). The level of the perturbations that will be introduced in the next training sessions will be increased (i.e., progression) according to the trainee’s ability (i.e., individualization) and based on the following cutoff value: if a trainee did not experience falls after perturbation, i.e., were caught by the safety harness system during the training session, and feels that he/she can be further challenged; if not, the same level of perturbation magnitude will be introduced again until he/she successfully recovers balance in the entire session. During the training, the trainee will be instructed to avoid a fall. To reduce the potential fear of falling, the trainee will be encouraged to focus on increasing the speed and length of the compensatory stepping reaction (i.e., awareness). The trainee will be encouraged to try to regain normal walking with a minimum number of steps (i.e., choosing a single-step strategy rather than a multiple-step strategy, which is associated with increased risk of falling); they will be able to follow the initial step with as many additional steps as required to regain their balance.

#### Augmented Feedback

The content and scheduling of augmented verbal feedback from the trainer will be designed to assist in initial problem solving and then faded to avoid the possibility that they might interfere with motor learning as skill level progresses, according to the CPF (Guadagnoli and Lee, 2004). Mansfield et al. (2017a) found that concurrent augmented visual feedback reduced electrodermal level with practice, while no feedback did not, suggesting that feedback may help to reduce anxiety. In our study, participants in both groups will be provided information regarding two aspects of the stepping reaction. The first will be knowledge of the results of the stepping reaction (the occurrence of a fall into the harness or not) through information inherent in the task (the pull of the harness). The second will be knowledge of the performance of the stepping reaction (e.g., length of the step, direction, and strategy). Verbal feedback by the treating physical trainer will be additionally provided, for example, “steps need to be faster” or “try stepping further”; in addition, they will be instructed to “go back as fast as they can to their normal rhythm of walking after each perturbation.” During each week of training, feedback will be faded by the trainer and only feedback inherent to the task (fall into the harness or not) will be available for problem solving and learning.

The instructions to the participants in both groups will be “walk at your preferred walking speed and react naturally if you lose your balance.” The treadmill speed will be adjusted to the participant’s preferred speed. The perturbations will have 18 levels of difficulty with increasing levels of perturbations (i.e., increased displacement, velocity, and accelerations of the longitudinal translations; see Figure 2, Table 3, details of the perturbation protocols used in the training program). In both groups, the subject’s activities will be documented in each session. Assistance and support will be used for anyone who feels uncomfortable in the initial phase of the training. It is important to note that these exercises will be customized to each subject’s ability. They will be designed to be challenging but never dangerous.

### Data Collection and Outcome Measures

To assess the feasibility of the study, we will document the number of training sessions attended/missed, reasons for missed sessions, and the rate of missing data for the outcomes described below. In case the participant did not attend more than two consecutive training sessions or four training sessions in total, they will be excluded from the study.

After signing on the consent forms, the participants will complete a questionnaire at baseline that asks about their demographics and medical history and past falls. Participant’s balance reactions will be assessed during standing and walking. Participants will be exposed to right/left/forward/backward unannounced platform translations through a mechatronic device (i.e., BaMPer system; Shapiro and Melzer, 2010) that will be increased systematically and controlled in six perturbation magnitudes in increasing level of difficulty (see Table 2), for a total of 24 perturbation trials in standing: six right, six left, six forward, and six backward. During the walking trials, the participants will be exposed to 12 perturbations, six right and six left, since recovery step initiation in the forward and backward perturbation trials in walking is hard to explore.

During the examination, participants will wear a safety harness that prevents falls but does not otherwise restrict their balance recovery movements. Fall during the assessment session will be defined as load cell sensors detecting 30% or more bodyweight suspended by the safety harness. Participants will wear their own walking shoes and be instructed to react naturally to keep their balance and to prevent themselves from falling in response to perturbations. In case of falling into the harness system, grasping the examiner’s hand, or asking to stop the test by the subject, the examination will be stopped and will not continue to the next level. A seated rest break will be given whenever needed. The data will be analyzed observationally and kinematically for each trial.

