**Figure 1 F1:**
[figure not shown]
Study flowchart.

**Table 1 T1:** Flowchart—overview of outcome measurements and time of assessment.

	T_0_	T_1_	T_T_	T_2_	T_3_
Recruitment	+				
Interview (in/exclusion)	+				
Consent form (and medical waiver)		+			
Balance assessment (balance reactions while standing and walking; postural stability)		+		+	
Randomization		+			
Questionnaires (BBS; MMSE; FES-1)		+		+	
Training documentation (perturbation progression; participant comments; adverse events)			+		
Fall monitoring					+
Satisfaction questionnaire				+	

*T_0_, prior to study; T_1_, baseline (pre-intervention); T_T_, training time; T_2_, post-intervention test; T_3_, follow-up (6 months post-intervention). Abbreviations: BBS, Berg Balance Scale; MMSE, Mini-Mental Scale Examination; FES-1, fear of fall questionnaire*.

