### Interventions

Block PBBT will be trained using a foretold magnitude and unidirectional perturbations during treadmill walking. The random PBBT will be trained using a computer-generated random multidirectional unexpected perturbation during treadmill walking. Each group will receive eight training sessions, twice a week for 4 weeks (Figure 2, Table 3, details of the training programs). Each session will last 20–30 min and will include 2 min of warm-up walking at participants’ preferred speed without any perturbations and 14–20 min of 35 unexpected perturbations while walking (based on the group motor learning technique). In the random PBBT, the perturbations will be given randomly every 20–40 s, and the training will end with a 2-min cool-down comfortable walking. The participants in the block PBBT group will be aware of the direction of the perturbation, given visual cues, and in each training session, only one perturbation direction will be trained. The goal of both training protocols (random PBBT and block PBBT) is mainly directed towards a cognitive understanding of the training and an improvement of self-confidence for exercises on higher perturbation magnitudes. Some general effects on muscle power and speed development, coordination, and conditioning (i.e., endurance) are expected. Everyone should progress to a higher perturbation magnitude (Figure 2, Table 3, the training programs).

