Sample sizes for each of the primary outcomes are outlined in Table 4. In regard to the fall threshold and the multiple-step threshold (backward), the sample size that was calculated for each group is similar, *n* = 19. A two-group one-sided 0.05 significance level *t*-test will have 80% power to reject the null hypothesis that the block PBBT and random PBBT are not noninferior [the difference in means of the fall threshold and multiple-step threshold (backward), μR − μB, is 2.00 and 1.90, respectively, or farther from zero in the same direction), in favor of the alternative hypothesis that the means of the two groups, i.e., block PBBT and random PBBT, are noninferior, assuming that the expected difference in means is 0.00 and the common standard deviation for the fall threshold is 2.40 and the common standard deviation is 2.00 for the multiple-step threshold (backward; based on an earlier study; Handelzalts et al., 2019). In regard to the multiple-step threshold (forward), the calculated sample size in each group is 8, and a two-group one-sided 0.05 significance level *t*-test will have 80% power to reject the null hypothesis that the block PBBT and random PBBT are not noninferior (the difference in means, μR − μB, is 1.90 or farther from zero in the same direction), in favor of the alternative hypothesis that the means of the two groups are noninferior, assuming that the expected difference in means is 0.00 and the common standard deviation is 1.40 (Table 2). To account for attrition rates reported to be about 25% involving training in older adults, (McMurdo et al., 2000) it was decided to include 25 participants in each group (19 × 1.25 = ~25) for a total of 50 participants.

**Table 4 T4:** Sample size estimation.

	Fall threshold	Multiple-step threshold (forward)	Multiple-step threshold (backward)
Test significance level α (one-sided)	0.05	0.05	0.05
Non-inferiority limit difference, Δ0	2.00	1.9	1.90
Expected difference, Δ1	0.00	0	0.00
Δ0 − Δ1	2.00	1.90	1.90
Common standard deviation, σ	2.40	1.4	2.0
Effect size, δ = |Δ0 − Δ1|/σ	0.833	1.357	0.826
Power, %	80	80	80
Sample size, per group, *n*	19	8	19

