### Statistical Analysis

Cohort descriptors and baseline values for primary and secondary outcomes will be compared between groups using Mann–Whitney *U* tests (continuous variables) or Fisher’s exact test (categorical variables). Measures that differ between groups at baseline may be used as covariates in the analysis of primary and secondary outcomes. To test the primary hypothesis, we will calculate the 95% CI for the post-intervention difference between groups (block PBBT minus random PBBT) for the primary outcomes [fall threshold and multiple-step threshold (backward and forward)]. Our hypothesis of non-inferiority will be supported if the lower limits of the 95% CIs are greater than the negative value of the non-inferiority limits (Schumi and Wittes, 2011). We will use both intention-to-treat and per-protocol analyses to test the primary hypothesis, as is recommended (Schumi and Wittes, 2011); per-protocol analysis will include only those participants who completed at least 80% of the training sessions. We will also use paired *t*-tests for each group individually to determine if the groups improve over time in the primary and secondary outcomes. To address the secondary objectives, we use analysis of covariance (ANCOVA) to compare the posttraining voluntary step execution test and postural sway parameters as well as the Berg Balance Score, Late-Life Function and Disability Index, and FES-I scores between groups, with the baseline value for each measure as a covariate. The dependent variable will be rank-transformed prior to conducting the ANCOVA to allow for nonparametric analysis.

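### Excluding randomised participants from the study for missed sessions contradicts the planned intention-to-treat test and leaves both primary analysis sets selected on attendance

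*Protocol article*

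**What the plan says.** The attendance rule stands in Data Collection and Outcome Measures, in a paragraph on feasibility: "did not attend more than two consecutive training sessions or four training sessions in total, they will be excluded from the study". The length of the course is given under Interventions: "Each group will receive eight training sessions, twice a week for 4 weeks". Table 1 marks randomisation at T1, and its legend gives the order of the time points: "T_1_, baseline (pre-intervention); T_T_, training time; T_2_, post-intervention test". Sessions can therefore be missed only after allocation.

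Statistical Analysis then says: "We will use both intention-to-treat and per-protocol analyses to test the primary hypothesis". It adds that "per-protocol analysis will include only those participants who completed at least 80% of the training sessions". The primary contrast is the block-minus-random difference after the intervention, so a participant without a T2 test has no observed primary outcome.

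The article does not say that a person excluded for attendance is still tested at T2 or stays in any analysis set. The Participants section deals separately with voluntary withdrawal and with withdrawal after a change in health. The attendance rule is thus a further route out of the study, and one that the investigators impose.

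**The concern.** Intention-to-treat keeps people in the arm to which they were allocated, whatever their attendance. A rule that removes randomised people because of attendance cannot be followed as written alongside such an analysis. What would carry the intention-to-treat name would be a second, looser per-protocol set.

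Two things are at stake. The first is the protection given by randomisation. Attendance arises after allocation and may depend on the arm: under Interventions, one schedule is foretold and in a single direction while the other is unexpected and multidirectional, and Limitations names dropout as a risk because the training is challenging. The second is the purpose of running two analyses. In a non-inferiority trial they are reported together because each has its own weakness. If both are filtered on the same variable, agreement between them reassures less. An analysis plan written later cannot recover T2 measurements that were never taken.

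**Working it through.** **1. The plan's own sample size.** For the fall threshold the inputs are a margin of 2.00 and SD of 2.40, an expected difference of 0, one-sided 0.05 and 80% power (Power and Sample Size Calculation, Table 4). The normal approximation, n = 2(1.645 + 0.842)² × 2.40² / 2.00² = 17.8, gives 18 per group. The t-test version gives 19, as stated, with power 80.9%. The article then inflates: 19 × 1.25 = 23.75, given as about 25. Dividing by 0.75 instead gives 25.3. The number enrolled is not at issue here. The allowance for loss is 25 − 19 = 6 per arm.

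**2. The per-protocol cut.** 0.80 × 8 = 6.4 sessions, so a participant must attend at least 7 of 8.

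**3. The exclusion rule.** More than two consecutive misses means a run of three or more. The part about four in total can be read as four or more missed (reading A) or more than four missed (reading B). Checking all 2⁸ = 256 patterns of attended and missed sessions:

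| Sessions attended | Patterns | Excluded, reading A | Excluded, reading B | Per-protocol |
|---|---|---|---|---|
| 0 to 3 | 93 | 93 | 93 | no |
| 4 | 70 | 70 | 25 | no |
| 5 | 56 | 6 | 6 | no |
| 6 | 28 | 0 | 0 | no |
| 7 or 8 | 9 | 0 | 0 | yes |

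These are counts of possible patterns, not probabilities. On reading A nobody with fewer than 5 sessions remains. On reading B nobody with fewer than 4 remains, and those with exactly 4 stay only if they never missed three in a row. The remaining set differs from the per-protocol set by a middle band: everyone attending 6, those attending 5 whose three misses were not consecutive and, on reading B, some attending 4.

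**4. Possible size of the bias.** Let p be the share of an arm excluded and g the amount by which retained people exceed excluded people on the outcome. The observed arm mean is then too high by p × g, and the block-minus-random difference is shifted by p_B × g_B − p_R × g_R. The document gives neither p nor g for attendance exclusions. For illustration, assume p of up to 6/25, the whole attrition allowance, and g = 2.0 levels, the fall-threshold gain in the earlier stroke study (4.5 to 6.5).

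- 6 excluded from block only: 6/25 × 2.0 = +0.48 levels, or 0.48/2.00 = 24% of the margin, in favour of block.
- 3 excluded from block only: 3/25 × 2.0 = +0.24 levels.
- 6 excluded from random only: −0.48 levels, against block.
- Equal shares and equal gaps: 0.

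**The case against.** The article does not say that T2 is withheld or that data are discarded. Exclusion from the study may have meant only the end of training, or withdrawal with the person kept in the intention-to-treat set as missing. The same paragraph promises to record missing outcome data, and such handling is often left to an analysis plan. This stands as a reason to call the passages irreconcilable as worded rather than to assert what the investigators will do. It does not remove the point: the rule is stated outright, and nothing says that these people are still measured.

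A reader might infer that the rule biases the trial towards non-inferiority. The document does not support that. The direction depends on which arm loses more people and how they would have fared. If unpredictable perturbations deter attendance, the exclusions would fall mainly in the random arm and work against block. Limitations describes difficulty in both arms and predicts no imbalance.

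A reader might also infer that intention-to-treat is the cautious analysis, spoiled by losing poor adherers. In non-inferiority, keeping poor adherers often pulls the arms together, which is why per-protocol is run alongside.

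Nor does the document support the idea that the excluded gained nothing. The Background cites lasting improvement after 24 perturbations in one session and says that few repetitions suffice. Four attended sessions at 35 each already give 140 perturbations.

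Finally, the two sets do not become identical; the middle band of attenders remains. The comparison is weakened, not emptied.

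**Conclusion.** The contradiction is real. An exclusion after randomisation that depends on adherence cannot stand beside an intention-to-treat test of the primary hypothesis. Followed as written, one set needs about 5 or more of 8 sessions (4 or more on the looser reading) and the other 7 or more. Neither preserves the randomised comparison, and they no longer serve as separate checks.

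This rests on taking exclusion from the study at its word, with no T2 test afterwards. Neither the direction nor the size of any bias can be determined from the document. The range of −0.48 to +0.48 levels is an illustration that needs all six exclusions in one arm and a 2.0-level gap. The 25% from which the six derive is attrition in general, not loss through this rule.

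**What to change.** Reconcile the two sections by separating the end of training from leaving the study. The attendance rule for training can stay as the investigators set it, but its wording should make clear whether it means four or more than four sessions.

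- Invite every randomised participant who has not withdrawn consent or been withdrawn for health reasons to the T2 test already planned, and analyse them in the allocated arm for intention-to-treat.
- Let attendance define only the per-protocol set, through the existing 80% rule.
- Count anyone already excluded without T2 in the intention-to-treat set as missing, report their number by arm, and give a sensitivity analysis for their outcomes.

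The last item matters because the article appeared on 25 February 2021 and Trial Status has T2 collection ending by 1 March 2021. For most participants the T2 window may have passed, so late invitations may be of little use.

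The cost is a change of wording, a few extra T2 visits where still possible, and some more analysis work. Retention also helps precision. For the fall threshold, with SD 2.40, margin 2.00 and true difference 0 all unchanged when poor attenders are included, 25 measured per arm give 82.3% power against the lower limit of a two-sided 95% interval; 19 give 70.5%.

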### Step Thresholds in Standing

We will verify single-step threshold, multiple-step threshold, and fall threshold levels, for AP and ML directions, following a loss of balance using the Vicon Motion Analysis Systems (Oxford, UK), allowing image pauses, slow motion, and running of the image back and forth. The single-step threshold level is defined as the minimum perturbation magnitude that consistently elicited a single compensatory step for at least two consecutive perturbation magnitudes. The multiple-step threshold is defined as the minimum perturbation magnitude that consistently elicited a sequence of recovery steps, and the fall threshold is defined as the minimum perturbation magnitude that consistently elicited a fall into the harness system. These step threshold levels were shown previously to be independent predictors of a future fall (Hilliard et al., 2008; Carty et al., 2015).

### Kinematics of Reactive Stepping

Three-dimensional (3D) kinematic data will be collected through the optical motion capture (Vicon Motion Systems, Oxford, UK), providing kinematic analysis of a motion sequence. Sixteen infrared cameras covered the lab space, mounted at a height of 2.6 ± 0.2 m, and provide a capture volume of 5.5 × 1.2 × 2.0 m^3^ evenly scattered approximately 4 m around the treadmill. The cameras operate and sample simultaneously, at a frequency of 200 Hz, the location of 39 reflective markers placed on anatomical landmarks of the body and another two on the moving platform (Figure 3). The markers are attached to a prepared whole-body flexible suit, which comes in several sizes to properly fit each subject. Views from the 16 cameras are mapped onto a 3D coordinate system by the computer (Vicon System Software) using an internal direct linear transformation algorithm. All perturbations are digitized, transformed, and smoothed using a low-pass filter (Butterworth second-order forward and backward passes) with a cutoff frequency of 5 Hz. The Vicon System was shown to be valid and reliable. Overall trueness (systematic deviations) of a dynamic reference object was −0.23 ± 0.35 mm (−0.24 ± 0.36%), and overall uncertainty (random deviations) for dynamic measurements was 1.11 ± 0.94 mm (1.16 ± 0.99%). For lower-body assessment (10 cameras, foot region) during walking, the mean trueness and uncertainty were −0.08 and 0.33 mm, respectively (Eichelberger et al., 2016).

The following kinematic parameters of reactive stepping in standing will be extracted: (1) the step initiation duration in milliseconds is calculated as the time from surface horizontal translation to foot lift off the ground and the step initiative; (2) the first recovery stepping duration (ms) is calculated as the time from surface translation to foot contact on the ground, completing the step; (3) the first reactive step length is calculated as the Euclidian distance in centimeters that the ankle markers displaced from step initiation to first step recovery; and (4) the center of mass (CoM) path displacement is calculated as the Euclidian distance in centimeters that the CoM displaced from step initiation to first step recovery. We rely on the 39-marker model of Vicon Motion Systems for the CoM position; (5) margin of stability (MoS) AP is defined as the AP distance between the XCoM-AP and the anterior boundary of the BoS, defined by the leading toe marker (either RTOE or LTOE for the right and the left feet, respectively); and (6) MoS-ML is defined as the ML distance between the XCoM-ML and the lateral boundary of the BoS, defined by the ankle marker (right ankle and left ankle for the right and the left feet, respectively).

Using the method above, we found excellent interobserver reliability for single-step threshold, multiple-step threshold, first-step recovery initiation duration, step duration, and step length [intraclass correlation coefficient (ICC)2,1 = 0.917, ICC2,1 = 0.975, ICC2,1 = 0.978, and ICC2,1 = 0.918, respectively; *p* < 0.001; Batcir et al., 2018].

The following parameters will be used to quantify balance recovery during walking trials: (1) step initiation time (ms) will be calculated as the time from surface translation to the first ML deviation (right or left) of the marker placed on the stepping leg ankle joint, more than 4 mm from the average baseline after the surface translation; (2) first recovery stepping duration (ms) will be calculated as the time from surface translation to foot contact on the ground; (3) first compensatory step length will be calculated as the Euclidian distance in centimeters that the ankle markers displaced from step initiation to first step recovery, i.e., foot contact; (4) first swing phase duration (ms) will be calculated from the step initiation time to when the foot contacted the ground, completing the first recovery step; and (5) the estimated distance of the CoM from the BoS (dBoS) is defined as the distance in ML direction (cm) of the estimated CoM (eCoM) from the theoretical edge of the BoS provided by the feet (i.e., the ankle marker) at the point of step initiation. A larger dBoS reflects a mechanically unstable condition at the point of first step initiation; i.e., the vertical projection of the eCoM at step initiation will be larger with respect to the BoS.

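### MoS-AP in standing is measured only to the front edge of the base of support, so it cannot be read as stability in backward losses of balance

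*Protocol article*

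**What the plan says.** The protocol article, under *Kinematics of Reactive Stepping*, lists six parameters to be extracted from reactive stepping in standing. The fifth is MoS-AP: "margin of stability (MoS) AP is defined as the AP distance between the XCoM-AP and the anterior boundary of the BoS". The marker is fixed as well, the boundary being "defined by the leading toe marker (either RTOE or LTOE for the right and the left feet, respectively"). No rear boundary is given, and the measure is not limited to forward losses of balance.

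The sideways counterpart is treated differently. "MoS-ML is defined as the ML distance between the XCoM-ML and the lateral boundary of the BoS", and the ankle markers of both feet are named, so either side can serve.

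*Data Collection and Outcome Measures* sets out the standing test "for a total of 24 perturbation trials in standing: six right, six left, six forward, and six backward". The note to Table 2 gives the same four directions at six magnitudes.

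The primary outcomes, in *Power and Sample Size Calculation* and *Statistical Analysis*, are the fall threshold and the multiple-step threshold. MoS-AP is not among them, nor among the measures listed for the secondary ANCOVA.

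**The concern.** A margin of stability is useful when it shrinks as the body nears the edge over which it may fall. Forward and backward platform translations unbalance a standing person in opposite directions, so one of the two AP sets must produce backward losses. For that set the front edge is the wrong reference. A participant who is being carried backward past the heels shows a large and growing distance to the toes.

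The consequence is one of interpretation. If between-group or pre-post differences in MoS-AP are reported for that set, a larger value does not mean a more stable participant. Backward reactive stepping belongs to the ability that this trial trains and tests, so a kinematic descriptor that cannot be read there loses much of its use.

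**Working it through.** The plan states no figure to reproduce. The check covers the trial count and the direction in which the measure moves.

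**Trials concerned.** Four directions × 6 magnitudes = 24 standing trials per assessment. Forward plus backward = 6 + 6 = 12 AP trials. One of the two sets gives backward losses: 6 of 12. This is a ceiling, for two reasons in the article. The examination does not go on to the next level after a fall into the harness, a grasp of the examiner's hand or a request to stop. The parameters also describe reactive steps, so a trial without a step may contribute nothing.

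**Feet in place.** Let x be the AP position of XCoM, T the leading toe and H the rearmost heel. I take the leading toe to be the foremost one, because it is said to define the anterior boundary.

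- Margin as written: A = T − x
- Margin to the rear edge: P = x − H
- Sum: A + P = T − H, which is constant while the feet do not move

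Every centimetre lost at the rear is therefore a centimetre gained in A, whatever the foot length. For illustration, assume H = 0 cm and T = 25 cm (the article gives no foot length).

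| Loss of balance | x (cm) | A = 25 − x (as written) | P = x − 0 |
|---|---|---|---|
| Backward | 6 | 19 | 6 |
| Backward | 2 | 23 | 2 |
| Backward | −2 | 27 | −2 |
| Backward | −6 | 31 | −6 |
| Forward | 12.5 | 12.5 | 12.5 |
| Forward | 20 | 5 | 20 |
| Forward | 24 | 1 | 24 |
| Forward | 28 | −3 | 28 |

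In the forward rows A falls as the front edge is approached and turns negative beyond it, as it should. In the backward rows A climbs from 19 to 31 cm while the margin that matters falls from 6 to −6 cm. All four backward values of A are positive, so taking A as signed or unsigned makes no difference to them.

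**After a backward step.** Suppose one foot steps back by L cm while the other stays. Then H becomes H − L and T is unchanged. With x = −2, P goes from −2 to L − 2, but A stays at 27. The step that restores the base leaves the measure where it was. If XCoM and the rear foot both move, A and P can change in the same or in opposite directions, so A has no fixed relation to rear stability.

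**The case against.** The strongest reply is that A is not wrong in itself: 27 cm is a correct distance to the front edge, and the article attaches no reading such as larger is better to MoS-AP. That stands, and it is why the point concerns the choice of boundary and not an inverted sign. It does not remove the point, because a margin of stability has no use except as a measure of stability. Nor is this a detail left to a fuller document: the article names both the boundary and the marker.

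Four stronger readings are tempting, and the documents support none of them.

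- **That dBoS, the walking measure, also points the wrong way.** It "is defined as the distance in ML direction (cm) of the estimated CoM (eCoM) from the theoretical edge of the BoS", and "A larger dBoS reflects a mechanically unstable condition at the point of first step initiation". If it were unsigned, with an assumed edge at 15 cm and the centre of mass at 5, 10, 14, 16 and 18 cm, it would read 10, 5, 1, 1 and 3, which is misleading inside the base. The article never says unsigned. Its explanation, that "the vertical projection of the eCoM at step initiation will be larger with respect to the BoS", fits outward excursion counted as positive: −10, −5, −1, +1, +3. On that reading larger does mean less stable throughout. A sign convention is something that a condensed article may leave out.
- **That MoS misleads whenever the centre of mass is inside the base.** It does not: in the forward rows it falls correctly from 12.5 to 5 to 1 cm.
- **That forward and backward trials will be pooled and cancel.** No section plans such pooling, and for the multiple-step threshold the article keeps the two directions apart.
- **That MoS-AP will contradict the threshold results by construction.** After a longer backward step with XCoM unchanged, the measure is merely insensitive. The article also gives the kinematics no role in explaining the thresholds.

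**Conclusion.** The definition is badly fixed for one of the two AP directions in standing. As written, MoS-AP increases when XCoM moves rearward and does not register a backward step that extends the base, so it cannot be read as stability in backward losses of balance. The extent is at most 6 of the 12 AP standing trials per assessment. It should not be quoted as a firm half, since the number of analysable trials depends on early stopping and on whether a step occurs.

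The direction of the effect follows from the geometry and not from the assumed 25 cm foot; only the centimetre values rest on that assumption.

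Materiality is limited. MoS-AP is a non-primary kinematic outcome and no named between-group analysis uses it. The sample size, the non-inferiority margins and the non-inferiority test are unaffected.

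**What to change.** Define MoS-AP against the boundary in the direction of balance loss:

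- forward losses: leading toe marker minus XCoM-AP;
- backward losses: XCoM-AP minus the rearmost heel marker, or the rearmost foot marker available in the 39-marker set, since the article does not name a heel marker;
- in both cases, negative means that XCoM lies outside the base.

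Classify trials by the direction in which balance is lost and not by the label of the platform movement, report the two directions separately, and give the number of analysable trials in each. Optionally, add one line stating that dBoS is signed with outside positive.

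The cost is a revised definition and a change to the processing script, best made before the groups are compared. The whole-body marker positions are already part of the planned motion capture, so no new trials, visits or participants are needed.
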